### Data collection

The demographic, baseline characteristics, and clinical outcome data will be collected in the clinics where the patients are treated. The questionnaires to assess treatment effects and physical conditions are to be completed by the patients after the treatment is completed. During the follow-up period, the participants are requested to return to the clinics to provide follow-up information and will be given subsidies to cover transportation and lost income based on the local minimum wage.

### Treatment regimen

Patients are required to receive eight to ten treatment sessions, at a frequency of two to three times a week. The intervention should be completed in 4 weeks.

### Interventions

The treatment scheme originates from the classical principles of traditional Chinese medicine and has been practiced in Guangdong Provincial Hospital of Chinese Medicine for some time. The final scheme was discussed and revised with the advice from a national expert committee of acupuncturists organized by the State Administration of Traditional Chinese Medicine (SATCM) of China. We hypothesized that OAT would have a specific effect on CS neck pain and be superior to both placebo and non-specific effects, therefore, two control groups were designed, in addition to the treatment group, as detailed below.

#### The optimized acupuncture therapy group

The treatment scheme for the OAT group consists of traditional acupuncture therapy, followed by intradermal needle therapy (INT). Nine acupuncture points were selected for the OAT group based on the advice and consensus of the national expert committee of acupuncturists detailed above. The name/code and location of the acupuncture points followed the WHO standards where possible [17-19], and are: Jianzhongshu (SI15, bilateral); Dazhui (GV14); Zhongzhu (TE3, bilateral); and Huatuojiaji (extra point; four points in two pairs, bilateral). The Huatuojiaji points are traditional Chinese acupuncture points, but are not listed in the WHO standard. To locate these four points, the acupuncturist needs to identify the cervical positive reaction planes by palpating the area 12.5 mm away from the patient’s cervical vertebra. If any tender points are found, the corresponding cervical vertebra level is considered the cervical positive reaction plane. The four Huatuojiaji points are located at the top ( upper Huatuojiaji) and bottom (lower Huatuojiaji) of th cervical positive reaction plane(s) bilaterally and 12.5 mm horizontally away from the corresponding cervical vertebra. If only one cervical positive reaction plane is identified, the practitioner should select a pair of the Huatuojiaji points on the cervical positive reaction plane and a second pair on the cervical vertebra next to the first pair.

The doctors performing all therapies have at least 5 years of acupuncture experience. Disposable stainless steel needles (0.3 mm × 40 mm; Suzhou Tianxie Acupuncture Instruments Co. Ltd, Su Zhou City, China) are used. The needles are inserted into the muscular tissue of the acupuncture points (to a depth of 20 mm) using the tube-guide method. The inserted needles are manually manipulated until the patient feels numbness or other acupuncture sensation (known as ‘de qi’), and the needles will be retained in the points for 20 minutes.

Following this tradition acupuncture therapyt, patients are treated by INT. There are two point selection schemes used alternatively: 1) the upper Huatuojiaji (bilateral) and Dazhui (GV14) and 2) the lower Huatuojiaji (bilateral) and Jianzhongshu (SI15; bilateral). Disposable stainless steel intradermal needles (0.22 mm × 5 mm; Suzhou Tianxie Acupuncture Instruments Co. Ltd.) are inserted into the skin to the subcutaneous tissue at an angle of 15 degrees to the point surface. The direction of needle insertion in Dazhui (GV14) is parallel to the spine, and in Huatuojiaji and Jianzhongshu (SI15), it is vertical to the spine. The inserted needles are fixed with medical tape, with their hilts remaining outside the skin, and will not be removed until the next treatment session.

#### The sham acupuncture group

Skin-penetrating shallow needles on sham points are used in the sham group. The location of the sham points is defined as 25 mm lateral to the standard location used in the OAT group: the sham point of Dazhui (GV14) is 25 mm vertically below the standard GV 14, the sham points of Jianzhongshu (SI15) and Huatuojiaji are 25 mm lateral to the standard SI15 and the corresponding points of Huatuojiaji, and the sham point of Zhongzhu (TE3) is 25 mm proximal to the standard Zhongzhu (TE3). The same type of disposable stainless-steel needles is used in the sham group as in the OAT group, therefore, the intervention in the sham group cannot be differentiated by needle appearance. The needles (0.22 mm × 40 mm) are inserted into the skin to a depth of 3 mm and remain at the subcutaneous level for 20 minutes. The doctor uses the tube-guide method, and any manipulation for acupuncture sensation or de qi is prohibited.

After sham acupuncture, the patients will be treated by point pressing. The point selection scheme is the same as for the INT in the OAT group. To ensure blinding, Semen Vaccariae (the seeds of the cow cockle, *Vaccaria hispanica*) are used to press on each point to conceal from the patient whether INT is being administered; as the points are all on the back, the patient cannot see what is being pressed on their skin.

#### The shallow acupuncture group

For the shallow group, the point selectionp is the same as for the OAT group; however, the doctor is required to insert the needles vertically to the subcutaneous level at a depth of no more than 3 mm. Any sensation (de qi) or needle manipulation is prohibited in this group. After acupuncture, the patients will also treated by INT using the same method as in the OAT group.

### Randomization

Randomization is performed using a central randomization interactive voice operating system (CRIVOS) developed by the Design, Measurement and Evaluation in Clinical Research (DME) centre of Guangzhou University of Chinese Medicine. The random allocation sequence was generated by an independent statistician from the DME centre using SAS software (SAS Institute, Cary, NC, USA), which was uploaded to CRIVOS. The doctors and researchers from all centers can connect to the CRIVOS system by telephone at any time to acquire the allocation result when they are enrolling participants. To enroll a patient, the doctor first confirms the patient qualifies for inclusion, then the doctor telephones the CRIVOS system and follows the voice instruction given, and finally, the doctor records the allocation information. There are three numbers indicating the allocation result: 001 represents the OAT group, 002 represents the shallow group, and 003 represents the sham group.

### Blinding

Because the efficacy of acupuncture inevitably depends on the skill of the operating doctors, allocation concealment to the doctors is not feasible for trials on acupuncture. Consequently, we applied a single-blind design in which the patients are blinded to their allocation. The statisticians are blinded to all treatment allocations throughout the study.. The concealment will not be broken until the final data analysis report is completed.

During and intervention phrase, the participants are treated with tube-guided needles that have the same appearance as the treatment needles. Similarly, use of the seeds in the sham acupuncture group gives the patient the sensation of a needle being inserted. Both the genuine acupuncture points and the sham points are in similar locations on the patients’ neck, back, and hands, and the participants cannot observe the manipulation performed during the treatment, therefore, the blinding should be effective.The requirements for the treatment sessions (the duration and frequency) are the same. After the second session and at the end of the treatment, participants are required to complete a questionnaire to assess the blinding.

### Outcomes

Three well-recognized patient-reported outcome (PRO) tools are used to measure the effect outcomes. The Northwick Park Neck Pain Questionnaire (NPQ) is used as the primary outcome measure, and the McGill Pain Questionnaire (MPQ) and the Medical Outcomes Study Short Form 36 (SF-36) are used as secondary outcome measures.

#### Primary outcome

The NPQ [20] is composed of nine items that measure: 1) neck-pain intensity, 2) relationship between neck pain and sleeping, 3) sensation of pins and needles in the arms at night, 4) duration of symptoms, 5) ability to carry items, 6) read and watch TV, 7) ability to work/perform housework, 8) ability to perform social activities (for example, doing leisure activities, visit friend.); and 9) ability to drive. The NPQ produces an overall percentage score, with a higher score reflecting a more serious disease state.

#### Secondary outcomes

The MPQ is a classic tool proposed by Melzack [21] for assessing the intensity of non-specific pain, and a higher MPQ score reflects more serious pain. The SF-36 is a general tool to measure medical outcomes and quality of life (QOL) [22,23]. The SF-36 consists of assessing outcomes in eight domains to represent patient QOL in physical, mental and social dimensions. A higher score reflects a better QOL in the corresponding domain.

In this trial, analgesic use is not recommended. Howver, based on bioethical considerations, the researchers will be able to provide free ibuprofen sustained-release capsules (Fenbid; GSK-China, Shanghai, China); State Food and Drugs Administration (China) registration number H10900089.) to the included subjects who request analgesic. The dose is 0.3 g (one capsule) orally, twice daily (morning and evening). The subjects’ analgesic use will be recorded and any use of analgesic beyond this will be considered a protocol violation.

#### Outcome measuring procedure and data collection

The outcomes will be assessed before the first treatment (baseline measurement), immediately after the final treatment (short-term outcome of therapeutic effect), and at the end of the first and third months after the final treatment (long-term effective outcomes). The data will be by PRO, with the questionnaires being completed by the participants themselves with necessary instruction from the researchers. Medication use at baseline, during the intervention, and at the 3-month follow-up will be recorded.

### Safety evaluation

Any expected and unexpected adverse events (AEs) will be recorded during the treatment. The expected AEs include local bleeding at the needle insertion points, and local numbness, pain, and dizziness during treatment. If any AE occurs, the doctor will provide corresponding treatment to the patient in accordance with the study protocol. The researcher will complete the adverse events/reaction form in the case report form and report the AE to the primary investigator and ethics committee immediately, who will make a decision on whether the patient needs to withdraw from the trial.

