**Methods/Design:**

This trial uses a multicentre, parallel-group, randomized, sham acupuncture and shallow acupuncture, controlled single-blind design. Nine hospitals are involved as trial centres. 945 patients who meet inclusion criteria are randomly assigned to receive optimized acupuncture therapy, sham acupuncture or shallow acupuncture by a computerized central randomization system. The interventions past for 4 weeks with eight to ten treatments in total. The group allocations and interventions are concealed to patients and statisticians. The Northwick Park Neck Pain Questionnaire (NPQ) is used as the primary outcome measure, and the McGill Pain Questionnaire (MPQ) and The Short Form (36) Health Survey (SF-36) are applied as secondary outcome measures. The evaluation is performed at baseline, at the end of the intervention, and at the end of the first month and the third month during follow-up. The statistical analyses will include baseline data comparison and repeated measures of analysis of variance (ANOVA) for primary and secondary outcomes of group and time differences. Adverse events (AEs) will be reported if they occur.

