### Trial status

Patients are currently being recruited into the study, and the follow-up is being conducted.

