### Statistical analyses

EpiData software (version 3.1 is used for data entry, and SPSS (version 16.0; SPSS Inc., Chicago, IL, USA) for statistical analyses. The analytic strategy includes the descriptive analysis of the demographic characteristics and the baseline data for the primary and secondary outcomes. The group differences are tested by analysis of variance (ANOVA) for continuous variables, the Kruskal-Wallis test for ranking variables, and the χ² test for categorical variables. The significance level is set at α = 0.05, two-sided.

There are four measuring points set to assess the efficacy of the OAT, as described above in the Outcomes section. Therefore, we will apply the two-factor repeated measures analysis of variance (ANOVA) model with the time of measure as the within-subjects factor and treatment as the between-subjects factor (significance level α = 0.05, two-sided). In addition, stratification analysis will be used to explore the potential effect difference between centres.

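### Adverse-event recording is set for the treatment period, and neither post-treatment visit is named for it: a small gap that is cheap to close

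*Protocol article*

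**What the plan says.** The protocol article gives a time window for adverse events (AEs) in one place, Safety evaluation: "Any expected and unexpected adverse events (AEs) will be recorded during the treatment". The same section describes what is anticipated: "The expected AEs include local bleeding at the needle insertion points, and local numbness, pain, and dizziness during treatment". The Abstract (Methods/Design) adds, with no window: "Adverse events (AEs) will be reported if they occur".

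Under Treatment regimen the course is eight to ten sessions within 4 weeks. Observation goes on well past that. Under Outcome measuring procedure and data collection, the assessments after baseline are "immediately after the final treatment (short-term outcome of therapeutic effect), and at the end of the first and third months after the final treatment". Besides the questionnaires, that section names one further item for follow-up: "Medication use at baseline, during the intervention, and at the 3-month follow-up will be recorded". Follow-up is in person; under Data collection, "the participants are requested to return to the clinics to provide follow-up information". The Statistical analyses section ties the visit schedule to benefit: "There are four measuring points set to assess the efficacy of the OAT". The trial is already running; under Trial status, "Patients are currently being recruited into the study, and the follow-up is being conducted".

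**The concern.** Two of the four measuring points fall after treatment ends, and the AE window as written stops before both. Patients come back to the clinic and are asked about pain, function, quality of life and, at three months, medication. No section says that they are asked about harms.

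What is at stake is how the safety results can be read. Benefit would be described up to three months after treatment and harm only for the 4-week course. If the final report showed no late AEs, a reader could not tell whether patients had none or were not asked. Safety evaluation covers unexpected events as well as expected ones, and unexpected events cannot be assumed to stop with the last session.

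**Working it through.** The plan gives no figure for this point, so there is none to reproduce. The check sets the relevant statements side by side, with some simple arithmetic.

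**1. Does any other statement extend the window?**

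| Section | What it covers | AE enquiry after treatment? |
|---|---|---|
| Safety evaluation | AEs, during treatment | No |
| Abstract, Methods/Design | AEs reported if they occur, no window | Permits a late report, plans no enquiry |
| Data collection | Return to clinic for follow-up information, content not listed | Not named |
| Outcome measuring procedure | Questionnaires at 1 and 3 months; medication use at 3 months | Not named |

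Post-treatment visits named for AEs: 0 of 2. Post-treatment visits named for medication use: 1 of 2.

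**2. Share of observation time covered.** Treatment is 4 weeks. Taking three months as 13 weeks (assumption), 4 / (4 + 13) = 4/17 = 24%. This is a share of weeks, not of harms.

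**3. Expected yield.** The expected events listed are bleeding, numbness, pain and dizziness. Post-treatment events among them: 0 of 4. The documents give no rate for late events.

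**4. One possible late event.** In the optimized and shallow groups, intradermal needles are taped in place and stay until the next session; the sham group has seeds pressed on the skin instead. Average days between sessions:

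- at three a week, 7/3 = 2.3; at two a week, 7/2 = 3.5
- check from the session count: 28/10 = 2.8 and 28/8 = 3.5

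Suppose needles are placed at the last session and stay in for that long. A skin reaction would then come after the end-of-treatment assessment, and the next planned visit is one month after the final treatment. An event while needles are still in might be read as during treatment; one that appears after removal could not.

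**5. Size of the fix.** The article gives two figures for required completers per arm:

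- Sample size calculation: 3 × 244 = 732 patients; 732 × 2 visits = 1,464 forms
- Discussion: 3 × 268 = 804 patients; 804 × 2 visits = 1,608 forms

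The number of patients already past these visits is not given, so the true count is lower by an unknown amount.

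**The case against.** The strongest reply is that this is a condensed article. Safety evaluation itself refers to the study protocol and to an AE form in the case report form, neither of which is shown, and those may collect AEs at follow-up. That stands as a limit on what can be said about trial conduct. It does not remove the point, because the article states a window rather than staying silent. If the full protocol goes further, the article's sentence is still the one to correct.

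Second, a treatment-period window suits the listed events, all of which are procedural. This stands, and it is why the priority is low.

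Third, persistent harm would not be invisible. The NPQ asks about pain intensity and pins and needles, and together with the MPQ and SF-36 it is completed at both follow-up visits. This partly stands: lasting pain, paraesthesia or loss of function would show by arm. A transient skin reaction would not.

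Fourth, asking about needle sites could lead sham patients to guess their allocation. This is a possible risk, not a demonstrated one, and it shapes the fix.

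Some stronger readings are tempting but unsupported:

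- *Late AEs would be barred from the report.* The Abstract's statement has no window, so spontaneous late reports remain possible.
- *Late harm is undercounted more in the two intradermal-needle arms.* A delayed local reaction is more plausible there, but the article does not establish that needles are placed at the last session, and it shows no difference in events between arms.
- *Efficacy conclusions are at risk.* Nothing in the AE window touches the primary outcome, the sample size or the primary analysis.

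**Conclusion.** The point holds in a limited form. As written, AE recording is set for the treatment period and neither post-treatment visit is named for it, so harms first appearing after the 4-week course are not systematically sought. The consequence is that the report could not separate absence of late harm from absence of enquiry.

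The expected gain from closing the gap is small, and the priority is optional to modest. The conclusion rests on the article's own text and would weaken if the full protocol or case report form collects AEs at follow-up. The 24% figure depends on counting three months as 13 weeks. The skin-reaction example depends on needles being placed at the last session.

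**What to change.** Amend Safety evaluation along these lines:

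> Expected and unexpected AEs are recorded from the first treatment to the three-month visit. From the date of this amendment, one open AE question, identical in the three arms and mentioning neither needles nor seeds, is asked at the one- and three-month visits after the NPQ, MPQ and SF-36 have been completed. AEs are reported by arm, with those first appearing after the final treatment shown separately, together with the number of patients actually asked at each visit in each arm.

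Asking after the questionnaires protects that visit's patient-reported outcomes. The one-month question still precedes the three-month questionnaires, so the neutral wording matters as well as the order. The number actually asked is needed because recruitment and follow-up are under way, and late data will be incomplete for patients already past these visits.

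The cost is a mid-trial amendment, one short form at two existing visits (at most about 1,464 to 1,608 forms for the planned completers), some reports unrelated to treatment, and a small residual risk to blinding. No visit is added, and the sample size and primary analysis do not change.

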### Sample size calculation

The size calculation is based on the mean and standard deviation (SD) for NPQ from a pilot study [1]. The reported pilot study was a two-arm design with a treatment group and one placebo group, whereas this trial protocol is a three-arm design with one treatment group (OAT) and two control groups (sham group and shallow group). The mean ± SD of the treatment group reported in the pilot study (20.71 ± S 11.91) [1] were used as the expected values of the OAT group, and the mean ± SD of the placebo group (24.04 ± 11.83) were used as the expected values of the two control groups. The software Power Analysis and Sample Size (PASS; version 11; NCSS Statistical Software, Kaysville, UT, USA) was used to perform the sample size calculation.

The sample size was calculated with a significance level of 0.05 and power of 0.90. The result was a total required sample size of 732, with 244 for each group. With a maximum dropout tolerance of 15%, 32 patients per center are needed for each group, or 94 patietns overall per center. Therefore, 846 patients are needed for the trial, with 288 for each group across the nine centers.

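### The stated 90% power matches a three-group omnibus test; for the hypothesis that OAT beats both controls, the same inputs give about 79% at 244 per arm and 83% at 268

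*Protocol article*

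**What the plan says.** The Interventions section of the protocol article hypothesises that "OAT would have a specific effect on CS neck pain and be superior to both placebo and non-specific effects", and gives this as the reason for having two control groups. The Discussion asks again whether OAT does better than the control treatments.

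The Sample size calculation section describes a "three-arm design with one treatment group (OAT) and two control groups (sham group and shallow group"). It takes its expected Northwick Park Neck Pain Questionnaire (NPQ) values from a two-arm pilot study: "The mean ± SD of the treatment group reported in the pilot study (20.71 ± S 11.91") for OAT, and "the mean ± SD of the placebo group (24.04 ± 11.83) were used as the expected values of the two control groups". It continues: "The sample size was calculated with a significance level of 0.05 and power of 0.90". The outcome is: "The result was a total required sample size of 732, with 244 for each group". The software is named; the statistical test is not.

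The Statistical analyses section plans ANOVA for group differences in continuous variables, and a two-factor repeated measures ANOVA with "treatment as the between-subjects factor (significance level α = 0.05, two-sided"). The article names no OAT-sham or OAT-shallow contrast. The Discussion gives a different size: 315 patients per arm, of whom at least 268 are to complete follow-up.

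**The concern.** The hypothesis has two parts: OAT better than sham, and OAT better than shallow. Both must be shown. An omnibus test of three means asks only whether the means differ somewhere, so rejecting it does not say which groups differ. It can reject because sham and shallow differ from each other, or because OAT beats one control and equals the other.

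If the 90% belongs to the omnibus test, the article states a power that is not the power of its own claim. The chance of missing that claim when the planning assumptions are true would then exceed the 10% that a reader takes from the Sample size calculation.

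**Working it through.** **Inputs (Sample size calculation and Statistical analyses).** NPQ means 20.71 (OAT), 24.04 (sham) and 24.04 (shallow), so the difference from OAT is 24.04 − 20.71 = 3.33. SDs are 11.91 (OAT) and 11.83 (controls). Groups are equal in size. On alpha, the analysis section says: "The significance level is set at α = 0.05, two-sided". Target power is 0.90.

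**Step 1: reproduce 244 per group.** For a one-way F test of three means, the noncentrality is λ = n × Σ(mean − grand mean)² / SD².

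- Grand mean = (20.71 + 24.04 + 24.04)/3 = 22.93.
- Deviations are −2.22, 1.11 and 1.11; the sum of squares is 4.9284 + 1.2321 + 1.2321 = 7.3926.
- With n = 244 and SD = 11.91, λ = 244 × 7.3926/141.848 = 12.716. The 5% critical value of F on 2 and 729 degrees of freedom is 3.008, and the power is 0.9002.
- With n = 243 the power is 0.8990. So 244 is the smallest n that reaches 90%, and 3 × 244 = 732.

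With SD between 11.83 and 11.87, the same test gives 241 to 243 per group. Other tests at 90% power do not give 244:

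| Test | n per group (SD 11.83 to 11.91) |
|---|---|
| Omnibus F, three groups | 241 to 244 |
| Two means, two-sided 0.05 | 266 to 269 |
| Two means, one-sided 0.05 | 217 to 220 |
| Two means, two-sided 0.025 (Bonferroni for two) | 314 to 318 |

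The Bonferroni version does give 244 at 80% power, but the stated power is 90%.

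**Step 2: power of one OAT-control comparison.** Normal approximation, two-sided 0.05: power = Φ(3.33/SE − 1.960), with SE = √((11.91² + 11.83²)/n) = √(281.797/n).

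- n = 244: SE = 1.0747; 3.33/SE = 3.099; power = Φ(1.139) = 0.873. The noncentral t gives 0.871.
- n = 268: SE = 1.0254; 3.33/SE = 3.247; power = Φ(1.287) = 0.901. The noncentral t gives 0.900.

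**Step 3: power of both comparisons.** The two statistics share the OAT arm, so their correlation is 11.91²/(11.91² + 11.83²) = 141.848/281.797 = 0.503. The bivariate normal probability that both exceed 1.960 is:

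- n = 244: 0.791. A simulation of 200,000 trials gave 0.792.
- n = 268: 0.834.

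In that simulation at 244 per arm the F test rejected in 90.3% of trials. In 11.5% of trials it rejected without both pairwise tests being significant in favour of OAT.

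**Step 4: what an omnibus rejection can mean.** Take means 20.71 (OAT), 20.71 (shallow) and 24.04 (sham), so that OAT has no advantage over shallow. The sum of squares is again 7.3926, λ is again 12.716, and the F test at 244 per group again rejects with probability 0.9002.

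**For scale.** At two-sided 0.05 each, 90% power for both comparisons needs about 318 evaluable patients per arm.

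**The case against.** **The test is inferred.** The article names software, not a method. This stands as a caveat, but an exact match at 244 (and not at 243), with no match from the pairwise alternatives at the stated power, makes the inference strong.

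**Contrasts are usual analysis-plan content.** A condensed article need not list them, and an unseen plan may do so. This stands: their absence alone would be no finding. It does not rescue the power statement. Adding two contrasts at 0.05 in another document would leave their joint power at 79% with 244 per arm.

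**The 79% is the least favourable figure.** With the Discussion's 268 completers, each comparison reaches about 90% and both reach 83%. Powering each comparison separately is also common in three-arm trials. Both points are fair, so the two sets of figures belong side by side.

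**The planned analysis uses repeated measures.** Its power may differ from that of a comparison at one time point. This also stands. The article gives no within-patient correlation, and its own calculation uses one mean per group.

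**Two stronger readings go too far.** A reader might infer an inflated type I error from two unadjusted comparisons. That would follow if either comparison alone counted as success with no prior F test, and the article states no such rule. With three groups, unadjusted pairwise tests made only after a significant F test keep the family-wise error at 5%. A reader might also infer that a significant F test will itself be reported as superiority to both controls. The article does not say so; Step 4 shows only what an omnibus test leaves open.

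**Conclusion.** The concern holds as a mismatch between the hypothesis and the powered test. The stated 90% is not the power to show OAT better than both controls, and the group test that the article names cannot establish that claim.

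Under the article's own assumptions, the chance of missing the claim is about 21% at 244 evaluable per arm and about 17% at 268, against the 10% implied. These figures assume that both controls share the pilot placebo mean, that the pilot SDs hold, that each test is two-sided at 0.05, and that a single time point is compared without adjustment. They are not the power of the repeated measures analysis. Which pair applies depends on which of the article's sample sizes is finally adopted.

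**What to change.** Name OAT-sham and OAT-shallow as the two primary contrasts, each tested at two-sided 0.05. Claim superiority to both controls only if both reject in favour of OAT. For that claim neither an alpha split nor a fixed testing order is needed, because requiring both rejections already controls the error. The omnibus test may stay as a description, but not as the basis of the claim.

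In the Sample size calculation, name the test that gave 244, and restate the power per contrast and jointly at the sample size finally adopted: about 87% and 79% at 244 evaluable per arm, or about 90% and 83% at 268. If power is to be quoted for the repeated measures model, state the assumed within-patient correlation.

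The cost is a less favourable power statement; no extra patients are needed. Recruitment is under way and the statisticians stay blinded until the final analysis report is complete, so the rule can still be fixed before allocation is revealed.
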